## Abstract

**Background and Objectives:**

Circulating tumor DNA (ctDNA)-based molecular residual disease (MRD) has been confirmed to predict postoperative recurrence of early-stage non-small-cell lung cancer (NSCLC), outperforming conventional imaging modalities by improving diagnostic efficiency and eliminating radiation-related risks. Integrating ctDNA with other liquid biopsy omics methods might further increase monitoring accuracy. In addition, patients with longitudinal undetectable MRD exhibit a favorable outcome and may be overtreated after radical surgery, while those traditionally not recommended for adjuvant treatment but with positive MRD may have not received appropriate disease management. This prospective real-world trial involving ten clinical centers across China aims to develop a multiomics noninvasive platform for recurrence prediction and to determine whether postoperative management guided by ctDNA is noninferior to standard care.

**Methods:**

We will recruit pathologically confirmed TNM stage IA-IIIA (8^th^ edition) NSCLC patients who are undergoing radical resection. Eligible participants will be divided into a standard treatment group and a ctDNA-guided group depending on their preference. Patients treated with or without neoadjuvant therapy will be studied in parallel. In the ctDNA-guided group, adjuvant therapy can be avoided for patients whose MRD is undetected at 1 month after surgery, and an additional requirement is to achieve a major pathological response for patients receiving neoadjuvant therapy. Imaging and MRD monitoring will be performed every 3–6 months for 3 years of follow-up, and postoperative management will be determined by the MRD results at each time point. Adjuvant therapy will be stopped if the patient's MRD status is continuously negative; otherwise, a treatment plan will be initiated after discussion among a multidisciplinary team (MDT). The recruitment phase began in April 2025, and 916 patients will be enrolled.

**Discussion:**

This prospective, multicenter, real-world study provides innovative techniques and is the first to confirm the instructive value of MRD for postoperative management of resectable NSCLC.

## Introduction

Lung cancer is among the malignancies with the highest mortality worldwide.^[1, 2]^ According to the 2011–2019 database from the International Association for the Study of Lung Cancer (IASLC), early-stage cases account for approximately 60% of non-small cell lung cancer (NSCLC).^[3]^ While curative surgery is the first-line treatment for these patients, more than 30% experience postoperative recurrence.^[4, 5]^ However, conventional imaging-based recurrence monitoring has reached a sensitivity bottleneck, with a reported false-positive rate of 17%–22%.^[6, 7]^ Multicenter clinical trials have shown that compared with X-ray, computed tomography (CT)-based surveillance does not improve patient outcomes. Recent studies further indicate that CT scans significantly increase the risk of brain and hematologic malignancies.^[8, 9]^ There is an urgent need for a more sensitive, noninvasive, and radiation-free approach to monitor postoperative progression.

Liquid biopsy-based minimal residual disease (MRD) detection is emerging as a precise tool for the postoperative management of solid tumors,^[10, 11]^ among which circulating tumor DNA (ctDNA) demonstrates promising roles in early-stage NSCLC.^[12]^ A positive state of ctDNA at a landmark (3 days–1 month after surgery) has shown hazard ratios of 2.9–43.4 for disease-free survival (DFS),^[13]^ and longitudinal monitoring achieves a higher sensitivity of 99.9% for relapse detection, with a median lead-time of 180–299 days compared with chest CT.^[14]^ However, the accuracy of ctDNA detection clearly decreases in patients with a low tumor burden or in nonshedders,^[14, 15]^ and the time point of blood sample collection during long-term surveillance is also not fully standardized. With the ongoing applications of other liquid biopsy omics methods in MRD detection, including plasma metabolomics,^[16]^ methylation,^[17]^ and fragmentomics,^[18]^ integrated approaches hold promise for further increasing the sensitivity of recurrence surveillance. Thus, the first step of this study aims to leverage multiomics technologies to establish a highly accurate and accessible MRD detection system for NSCLC.

As for adjuvant therapy, the overall aim is to improve patient survival without unacceptable diminishment of quality of life (QoL).^[19]^ However, TNM staging-based strategies are relatively homogeneous and fail to fit all patients. For NSCLC patients with EGFR-sensitive mutations in stages IB-IIIA, the National Comprehensive Cancer Network (NCCN) guidelines recommend 3-year adjuvant TKI therapy.^[20]^ Nonetheless, the ADAURA study revealed that 33% of patients in the control group remained disease free for 5 years,^[21]^ suggesting overtreatment in some patients. Additionally, increased relapses post-TKI discontinuation also imply a suboptimal treatment duration.^[22]^ A similar issue applies to driver-negative cases. In addition, the indication for adjuvant therapy in patients who achieve pathological complete response (pCR) following neoadjuvant treatment remains controversial.^[23]^ More precise adjuvant treatment strategies are needed.

Given the monitoring efficacy of ctDNA, investigators have explored novel modalities of ctDNA-guided intensification/de-escalation for standard treatment (adaptive adjuvant therapy). A randomized controlled trial for colorectal cancer has proven the feasibility of ctDNA-guided reduction in adjuvant chemotherapy without compromising survival.^[24]^ In advanced NSCLC, an adaptive de-escalation TKI strategy for patients with no lesions after local consolidation therapy and a negative ctDNA test result is feasible.^[25]^ Although exploratory analyses in early-stage NSCLC suggest that only patients with positive ctDNA results may benefit from adjuvant therapy,^[26, 27]^ whether a ctDNA-guided adaptive strategy is suitable for routine clinical practice in the postoperative setting remains unclear. Therefore, this MRD-based modality will be evaluated in the second step of this study. Through this multicenter real-world observational-interventional study design, we aim to establish the first noninvasive and systemic strategies for the precise postoperative management of NSCLC.

## Overview of the study design

This study includes two interlinked parts: an observational substudy and a prospective interventional substudy. Patients will be recruited from 10 tertiary clinical centers in China (Table 1), including stage IA-IIIA NSCLC patients who are initially treated or receiving neoadjuvant therapy. Each site has a high volume of eligible patients (> 1000 patients with early-stage NSCLC each year) and has expertise in enrolling patients and the ability to collect and store biospecimens. Patients will be followed after surgery, and blood collection will be performed at prespecified time points.

**Table 1 j_jtim-2026-0023_tab_001:** Medical centers of the REMODEL study

Peking University People’s Hospital
Guangdong Provincial People’s Hospital
Jiangsu Cancer Hospital
Shanghai Chest Hospital
The Second Xiangya Hospital, Central South University
Shenzhen Third People’s Hospital
Zhongshan Hospital, Fudan University
Peking University First Hospital
Wuhan Union Hospital
Shandong Cancer Hospital

The observational substudy aims to develop a novel multidimensional approach for noninvasive postoperative recurrence monitoring of NSCLC by innovatively integrating multiomics data, including clinicopathological features, plasma metabolomics, proteomics, cell-free DNA (cfDNA) features and radiomics, through artificial intelligence algorithms. Model development will leverage perioperative blood samples from early-stage NSCLC patients in a retrospective cohort, with external validation performed using samples of prospectively recruited patients.

The prospective interventional substudy will evaluate the feasibility, safety and clinical efficacy of ctDNA-MRD-based treatment intensification/de-escalation strategies in real-world settings while exploring the association between postoperative ctDNA-MRD monitoring dynamics and clinical outcomes. We will divide patients into standard treatment and ctDNA-MRD-guided groups, primarily comparing the two-year DFS rate and the total cost of treatment 24 months post-operative, as well as externally validating the sensitivity of the novel monitoring method established by the observational substudy.

## Objectives

### The primary aims of this study are as follows:

(1) To develop a novel multidimensional approach with increased sensitivity for noninvasive postoperative recurrence monitoring of NSCLC;

(2) To establish a ctDNA-MRD-guided postoperative management modality for NSCLC patients;

(3) To establish a national database and a sustainable digital platform for postoperative tracking of NSCLC.

Secondary aims of interest include the following:

(1) To explore the association between ctDNA changes during adjuvant therapy and patient outcomes;

(2) To investigate the association between ctDNA features and patient outcomes in the neoadjuvant setting.

## Observational substudy: A novel multiomics noninvasive platform to monitor postoperative recurrence

### Settings

This observational substudy comprises retrospective and prospective components (Figure 1). The retrospective cohort of 200 treatment-naive NSCLC patients and 100 matched cancer-free adults was derived from the previously established Pulmonary Nodule Plasma Proteomic and Metabolomic Database of Peking University People’s Hospital (Ethics Approval No. 2021PHB150-001; ClinicalTrials.gov Identifier: NCT04948047), while the prospective cohort of 160 NSCLC patients will be consecutively enrolled from the same institution. First, we will screen novel MRD biomarkers in the retrospective cohort and perform exploratory recurrence detection modelling that integrates clinicopathological features, plasma metabolomics, proteomics, cfDNA signatures and radiomics. We will subsequently internally validate the new model on prospective components and further conduct external validation using samples from the interventional substudy.

**Figure 1 j_jtim-2026-0023_fig_001:**
[figure not shown]
Design of the observational substudy. The retrospective cohort comprises healthy controls (*n* = 100) and NSCLC patients (*n* = 200). This cohort will be used to establish a noninvasive platform for postoperative recurrence monitoring, and AI-based integration of ctDNA, radiomic features, and novel biomarkers identified through metabolomics and proteomics analysis will be leveraged. Internal validation will be performed using the prospective cohort from the observational substudy (*n* = 160), with external validation conducted through the multicenter interventional substudy (*n* = 400; see the intervention substudy section for details).

### Patient enrollment

The inclusion and exclusion criteria are listed in Table 2. Patients will be identified and enrolled by clinics at the enrollment sites. During the clinic visit or hospitalization, the clinical researcher will confirm eligibility, ensure that the patient provides informed consent, and collect relevant study data and blood samples.

**Table 2 j_jtim-2026-0023_tab_002:** Inclusion and exclusion criteria for the observational substudy

**Retrospective enrollment of cancer-free individuals (*n* = 100)**	
Inclusion	
	(a) Age ≥18 years;
	(b) No systemic or metabolic diseases;
	(c) Signed informed consent.
**Retrospective enrollment of patients with NSCLC (*n* = 200)**	
Inclusion	
	(a) Adults (≥18 years) with pathologically confirmed TNM stage IA-IIIA (8th edition) NSCLC that are undergoing radical surgery;
	(b) Availability of matched tumor tissue, blood samples and accessible imaging records;
	(c) No history of other malignancies within the past 5 years;
	(d) No neoadjuvant therapy;
	(e) Signed informed consent.
**Prospective enrollment of patients with NSCLC (*n* = 160)**	
Inclusion	
	(a) Adults (≥18 years) with clinical TNM stage IA-IIIA (the 8th edition) NSCLC that are scheduled for radical surgery;
	(b) Radiologically confirmed solid lesions with diameters ≥1 cm * or ground-glass nodules (GGN) with short-axis diameters ≥1.5 cm;
	(c) Signed informed consent.
Exclusion	
	(a) Pure GGN observed via chest CT;
	(b) History of any other malignancy within 5 years;
	(c) Has active infectious diseases;
	(d) Failure to undergo radical surgery;
	(e) Pathologically confirmed non-NSCLC;
	(f) Pathologically confirmed TNM stage IIIB-IV (8th edition);
	(g) Life expectancy less than 12 weeks.

^*^Solid lesions with long-axis diameters measuring 1–1.5 cm also require short-axis diameters ≥1 cm to preserve adequate samples for baseline detection. NSCLC: non-small cell lung cancer; GGN: ground-glass nodule; CT: computed tomography.

### Data and sample collection

#### Data collection

Demographic characteristics, clinical profiles, and preoperative images will be obtained through electronic medical record review. Comprehensive documentation includes treatment details (surgical procedures and adjuvant therapy), therapeutic efficacy, and treatment-related adverse events. Pathological data from surgical specimens, along with postoperative imaging examinations and prognostic outcomes during follow-up, will be prospectively recorded in a centralized research database.

#### Collection and storage of biospecimens

Twenty-four milliliters of preoperative blood samples and matched tissue specimens (for customized MRD sequencing panel development) will be collected. Venous blood will be allocated as follows: 4 mL will be transferred to EDTA-coated tubes for plasma metabolomic and proteomic profiling (processed within 2 h with protease inhibitor cocktail addition after centrifugation), and 20 mL will be transferred to Streck cell-free DNA BCT tubes for ctDNA analysis (centrifuged within 72 h). Equal-volume samples will be taken from one side of the tumor using a skin perforator. For smaller tumors, researchers will consider sampling from various locations on the opposite side. Samples from at least two tumor regions will be separated by 0.3 cm to 1.0 cm, depending on the tumor size. Border samples will be collected at the tumor margin to ensure that both tumor and normal samples are obtained. Paired normal tissue will be taken at least 2 cm from the tumor edge. Finally, the central coordinates of each sampling point will be recorded using a double-scale square and documented with photographs. All aliquots will be cryopreserved at −80 °C until batch analysis.

### Data analysis

#### Multiomics profiling

Multiomics profiling, including radiomics-based recurrence prediction, nontargeted plasma metabolomics and proteomics, cfDNA methylation and genomic feature analysis, and individualized ctDNA detection, will be conducted. The detailed methods are provided in Supplementary material 1.

#### Optimization of plasma proteomic and metabolomic features characterizing lung cancer lesions

In the retrospective cohort, we will perform untargeted proteomic and metabolomic profiling on plasma samples from lung cancer patients and healthy controls to identify lung cancer-associated signatures as potential MRD biomarkers. Initial selection will be performed using the Wilcoxon rank-sum test with FDR correction (adjusted *P* < 0.05). Candidate selection criteria include mass spectrometry-detectable features with stable retention time, reproducible peak intensity, interpretable fragmentation patterns, and clinically relevant half-life, optimized through machine learning algorithms.

For model-driven feature optimization, the differential molecules will be first evaluated for their contribution to classification using a support vector machine (SVM) model, and the top 100 features will be sequentially added according to their importance scores to construct stepwise classification models. At each step, model performance will be evaluated using fourfold cross-validation, which will be repeated 500 times to ensure stability and robustness. The average classification accuracy across all iterations will be used to determine the optimal number of features for each omics layer. Based on the point of peak model performance and cross-validation consistency, a final subset of 30 to 50 informative features will be selected and used for downstream integration. This two-stage process is designed to balance dimensionality reduction with predictive efficiency and biological interpretability.

#### Development and validation of a multidimensional model for noninvasive recurrence prediction

This study will employ a semisupervised DeepProg framework^[28]^ to synthesize plasma metabolomic/proteomic profiles, radiomic recurrence scores, and multianalyte cfDNA features in the retrospective patient cohort. The semisupervised DeepProg framework combines autoencoder-based dimensionality reduction and Cox proportional hazards modeling. For each omics layer, the top-ranked features will be preselected on the basis of univariate survival associations and effect sizes. These features will be embedded into latent representations using separate autoencoders and then fused into a unified risk prediction model. The DeepProg architecture allows the integration of incomplete data across layers and enables survival risk stratification based on molecular profiles. The final prognostic model will combine multidimensional risk scores with TNM staging through Cox proportional hazards regression. A threshold for recurrence risk stratification will be optimized in the training cohort to categorize patients into high- and low-risk groups, and its prognostic utility will be validated in the test and validation cohorts *via* Kaplan^‒^Meier analysis. We will also assess the sensitivity, specificity, accuracy and C-index. The model will be externally and respectively validated on a prospective patient cohort and a multicenter cohort from subsequent phases of this study to confirm its reproducibility and generalizability.

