#### Sample size calculation

Sample size determination was guided by a literature review and practical considerations, with 200 lung cancer patients and 100 healthy controls enrolled retrospectively for prediction model development. The sample size of the independent prospective cohort should consider recurrence prediction validation and 2-year DFS comparisons. On the basis of the calculations in Supplementary material 2, we plan to prospectively enroll 160 patients. Enrollment continuation will be determined by the investigator after the predefined sample size is met.

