### Outcomes

The primary endpoint of this clinical trial is the two-year DFS rate after surgery, defined as the interval from the surgical date to objectively confirmed disease recurrence or death from any cause.

Secondary outcomes of interest include (1) overall survival (OS), (2) total treatment cost 24 months after surgery, (3) incremental cost effectiveness ratio (ICER), (4) sensitivity of the novel recurrence prediction model developed in the observational substudy, (5) timely diagnosis of recurrence in the new follow-up model developed by the observational substudy, and (6) ctDNA characterization during neoadjuvant/adjuvant therapy and its associations with clinical outcomes, including short-term efficacy (radiological and pathological response) and long-term survival. Total treatment cost refers to the expense of lung cancer-related treatment for the patient during the research period, including the drug cost, follow-up treatment cost, drug management cost (consultation fee, antitumor drug allocation fee, intravenous infusion fee, nursing fee, *etc*.), cost of follow-up laboratory tests and imaging, and management cost of adverse reactions of grade 3 or greater, with an incidence rate of more than 5%.

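### Validation of the multiomics model uses only single-model results for a score that already contains TNM stage and ctDNA, so as described it cannot show the increased sensitivity of primary aim (1)

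*Protocol article*

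**What the plan says.** Under Objectives, primary aim (1) is "To develop a novel multidimensional approach with increased sensitivity for noninvasive postoperative recurrence monitoring of NSCLC". The Introduction motivates it in two ways: imaging surveillance has limited sensitivity, and ctDNA loses accuracy when tumor burden is low or the tumor does not shed.

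The section on development and validation of the multidimensional model fuses plasma metabolomic and proteomic profiles, "radiomic recurrence scores, and multianalyte cfDNA features in the retrospective patient cohort". The Figure 1 caption confirms that "AI-based integration of ctDNA, radiomic features, and novel biomarkers identified through metabolomics and proteomics analysis will be leveraged". Stage is then added: "The final prognostic model will combine multidimensional risk scores with TNM staging through Cox proportional hazards regression". A risk threshold is optimized in the training cohort, and "its prognostic utility will be validated in the test and validation cohorts" by Kaplan-Meier analysis. The section continues: "We will also assess the sensitivity, specificity, accuracy and C-index".

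In the interventional substudy, secondary outcome (4) is the "sensitivity of the novel recurrence prediction model developed in the observational substudy". The sample size section describes the development set as "with 200 lung cancer patients and 100 healthy controls enrolled retrospectively for prediction model development". Validation uses 160 prospective patients and a multicenter cohort, given as 400 in the Figure 1 caption.

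None of these places names a reference model, a comparator for sensitivity or a measure of added value.

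**The concern.** The aim is comparative, but the validation results described are not. A Kaplan-Meier split of the final score asks whether the whole score, stage and ctDNA included, is related to disease-free survival. The aim asks whether the new layers detect more than is already available. These questions have different answers when the known markers carry the prognosis.

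The listed accuracy measures do not close the gap, because each belongs to the one combined model. A sensitivity figure on its own cannot show an increase, and one read at a threshold optimized for that model can be raised by giving up specificity.

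At stake is the headline claim of the observational substudy. A score driven by stage and ctDNA could be presented as a validated multiomics platform while the contribution of the metabolomic, proteomic and radiomic layers remained unknown.

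**Working it through.** **Plan's own figure.** The 160 cannot be reproduced, because its calculation is in Supplementary material 2, which is not at hand. The totals agree: 160 + 756 = 916 and 609 + 147 = 756.

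**Inputs from the article.** Development n = 200 patients; validation n = 160 and n = 400; recurrence above 30% (Introduction; 30% used); landmark ctDNA hazard ratio 2.9 to 43.4 (Introduction; lowest value used); two-sided 0.05 (Statistical analysis).

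**Step 1. How easily does ctDNA alone separate two groups?** With d events and a proportion p at high risk (Schoenfeld):

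power = Φ(√(d·p·(1−p))·ln HR − 1.96), with ln 2.9 = 1.065.

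- n = 160: d = 160 × 0.30 = 48. For p = 0.2, √(48 × 0.16) × 1.065 − 1.96 = 0.99, so power is 84%. For p = 0.1, 0.3 and 0.5 it is 60%, 92% and 96%.
- n = 400: d = 400 × 0.30 = 120. Power is 94% at p = 0.1 and over 99% for p = 0.2 to 0.5.

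**Step 2. Full procedure with omics that are pure noise.** Train on 200, lock the score and threshold, apply them to new patients, and compare high with low risk by log-rank test. Two simulations used different assumptions.

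*Simulation A* (500 runs; 35% stage II-IIIA, 20% ctDNA-positive, five noise features, threshold chosen by maximum log-rank). Share of runs with p < 0.05:

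| True effects | n = 160, 15% / 30% events | n = 400, 15% / 30% events |
|---|---|---|
| Stage HR 2 | 19% / 36% | 34% / 66% |
| Stage HR 3 | 49% / 83% | 78% / 99% |
| Stage HR 2, ctDNA HR 2.9 | 47% / 81% | 80% / 99% |

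A control run with stage HR 1 gave 3.4% to 5.4%. A test of the noise score adjusted for stage (and ctDNA) stayed at about 3% to 7%.

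*Simulation B* (600 runs; stage mix 60/20/20%, ctDNA-positive in 8/20/35% by stage, one noise score, top 30% high risk, ctDNA HR 2.9):

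- Stage HR 1.8 per step, 30% recurrence: 98% at n = 160, over 99% at n = 400. At 20% recurrence: 95% and over 99%.
- No stage effect, 30% recurrence: 56% and 91%.
- Mean C-index gain over stage plus ctDNA: −0.004 to 0.000 in every setting.

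The spread between A and B shows how far the rates depend on assumptions. The direction does not change: the split separates, while the adjusted test or C-index difference shows that the omics add nothing.

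**Step 3. Sensitivity without matched specificity.** Assume ctDNA has 50% sensitivity and 95% specificity, 30% events, and a threshold set by Youden's index in development. Adding stage and noise gave a sensitivity above that of ctDNA in 88% (n = 160) and 94% (n = 400) of runs. The mean gain was 15 points, and specificity fell by 14 points. With ctDNA sensitivity of 30% the share was over 99%; with 70% it was 49% to 61%.

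**Step 4. What a paired sensitivity comparison can deliver.** Only relapsing patients contribute. Exact McNemar power, with the reference alone detecting 5% of relapses (assumed):

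| Recurrence | Relapses, n = 160 / 400 | Gain of 15 points (20% v 5%) | Gain of 10 points (15% v 5%) |
|---|---|---|---|
| 20% | 32 / 80 | 26% / 74% | 11% / 44% |
| 30% | 48 / 120 | 46% / 90% | 23% / 63% |
| 40% | 64 / 160 | 62% / 97% | 33% / 78% |

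If half of the 400 were standard-arm patients, all MRD-tested (an assumption), 200 × 0.30 = 60 relapses would remain. Power for a 15-point gain would then lie between the values for 48 and 64 relapses, 46% and 62%.

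**The case against.** The strongest reply is that the article describes ordinary validation of a complete model, whose stated purpose is reproducibility and generalizability. For that purpose a significant split is a correct result, since the combined score really is prognostic. A reader might infer that the plan would declare the platform validated on a log-rank p < 0.05, and read the simulated percentages as false-positive rates. The documents do not support this: the model section sets no such pass rule.

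A reader might also infer that increased sensitivity is tested nowhere. That cannot be established. The article refers outcome analysis and sample size to supplements that are not at hand, and a comparator could be named there.

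Imaging is as well supported a comparator as ctDNA, since both the Introduction and the closing Discussion cite the sensitivity limits of imaging. Stage and score do enter one Cox model in development, but no stage-adjusted result is described for the validation cohorts.

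The inputs to the magnitudes are also open to challenge. The hazard ratio of 2.9 is a postoperative landmark value, while the observational substudy describes preoperative blood. The article's one ctDNA sensitivity figure, 99.9% for longitudinal monitoring, would leave almost no room for a gain.

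What stands is narrower. The model section sets out its validation measures itself, and none of them compares the model with anything.

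**Conclusion.** The point holds in limited form. As the article describes it, the validation can show that the combined score is prognostic. It cannot show that the new layers add to stage and ctDNA, or that sensitivity is increased. This follows from the structure of the comparison and needs no simulation.

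The simulations show only that the gap can matter in practice: with prognostic stage and/or ctDNA and worthless omics, separation at p < 0.05 occurred in 19% to 98% of runs at n = 160 and 34% to over 99% at n = 400. These figures rest on assumed stage mix, ctDNA prevalence, stage hazard ratios and event rates. Step 3 rests further on an assumed ctDNA sensitivity and a threshold rule that the article does not specify.

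**What to change.** 1. Keep the Kaplan-Meier curves and single-model metrics as description.
2. In both validation cohorts, evaluate the locked multiomics score (without TNM) in a Cox model containing TNM, and in one containing TNM plus ctDNA. Report the C-index difference from those reference models, fitted in the same development cohort, with a 95% CI. The second comparison bears on the new layers, because the score itself contains ctDNA.
3. Name the comparator for increased sensitivity: ctDNA alone, and imaging if that is intended. Report the paired difference in sensitivity with a 95% CI, at a threshold locked in development to match the comparator's specificity.
4. Base that claim mainly on the multicenter cohort and treat the 160-patient result as supportive, since only about 48 relapses are expected there at 30% recurrence. Requiring success in both cohorts would often miss a real gain.
5. For the comparison with ctDNA, use mainly MRD-tested standard-arm patients, or report by arm. In the guided arm a positive ctDNA result triggers treatment, which can change who relapses. Control-arm results may be disclosed on request after 6 months, so disclosure should be recorded.

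The cost is analysis wording and a few extra model fits, with no new patients, samples or assays. A favourable claim becomes harder to reach, and restricting to the standard arm reduces the number of relapses and so the precision.
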